**Fig. 1 Fig1:**
[figure not shown]
Flowchart of Thirsty Choose Water study

### Intervention design

The interventions delivered in this study include a behavioural intervention and the installation and promotion of chilled water stations. Following randomisation, schools will be informed of the study arm to which they have been allocated and the project team will work with the school to progress the allocated intervention.

Schools allocated to the behavioural intervention (Arms 1 and 3) will receive health messages regarding SSBs and the promotion of water as a preferred drink through each domain of the Health Promoting Schools Framework (Additional file 1). Within the curriculum, teaching and learning domain students will receive the intervention through the inclusion of messages in year 7 Personal Development, Health and Physical Activity (PDHPE) lessons and through the TCW website which provides a range of relevant resources. Two PDHPE lesson plans and resources pack have been developed in consultation with PDHPE teachers. These lesson plans outline the key water messages as well as a goal based activity for students to decrease their consumption of SSBs and increase their water consumption. To support the implementation of these lesson plans within the PDHPE curriculum professional development opportunities for teaching staff will also be provided.

The school organisation ethos and environment domain will be addressed by messaging through posters, school newsletters, school social media and other opportunities identified locally by schools to engage students and their families (potentially reaching students in other years). The partnerships and services domain will be addressed through a partnership between schools and local immunisation teams, providing an opportunistic avenue for the TCW messages to be further targeted to year 7 students. Post-immunisation students will participate in the Spouts and Straws game (see Additional file 2), trialled in the project pilot. The TCW - BI intervention will occur from July to December, commencing with the curriculum delivery, and with messages being reinforced trough the school organisation ethos and environment domain and then through the immunisation component.

Schools in Arm 2 and 3 will receive a chilled water station. The installation of chilled water stations in will occur once baseline data has been collected. Local consultation with schools will determine the most appropriate location for the chilled water station, which has access to water, power and drainage. A remote water monitoring system will be added so that the flow of water from these chilled water stations can be recorded. Schools in Arm 3 will receive both interventions. Schools in Arm 4 will be the control group and will receive neither of these interventions, but will complete baseline, post and follow-up measures.

### Outcomes

The primary outcome for the study is self-reported water consumption, with a 5% increase in the proportion of year 7 students drinking 5 or more cups of water per day. This measure is based on data from the 2011 School Students Health Behaviour Survey [8]. The secondary outcome is students’ knowledge, attitudes and consumption of SSBs. See Table 1.

**Table 1 Tab1:** Primary and Secondary outcomes

Primary Outcome	Secondary Outcome
• Consumption of water	• Students’ knowledge and attitudes regarding water consumption • Students’ knowledge regarding SSBs • Students’ attitudes regarding SSBs consumption • Students’ consumption of SSBs • Students’ purchasing of SSBs • The school environment eg promotion of water messages, reduced access to SSBs

### Data collection

Data collected will include student, water flow and school level data. Student data will be collected from year 7 students at three time points: baseline, post intervention, and at follow-up. Student data will be collected by an online survey monkey or a paper based survey administered in class, dependent on school facilities and resources. Identical surveys will be administered at each time point with additional process evaluation questions at follow-up. A unique identifier (initials and DOB) will be generated in order to match pre- and post-intervention data.

The student survey is composed of items adapted from existing validated survey instruments [19] that will measure students self-reported: Knowledge about consuming water and SSBs; Attitudes towards consuming water and SSBs; Self-reported consumption of water and SSBs; their purchasing of SSBs.

Water flow data will be collected through the installation of water meters and data loggers on chilled water stations to provide an objective measure of water consumed over time. Water meter data will be collected remotely and recorded continuously in real time.

School level data will be collected through a school profile and an environmental scan. School profile data will include information on the type of school (eg Public, Catholic and Independent), size of school (total number and composition of students), the schools Family Occupation and Education Index (FOEI)(a school level index of educational disadvantage related to socioeconomic background) whether the canteen is private or school run and whether the school has vending machines. Students’ access to bottled water and SSBs through environmental scans of the school setting will also occur by identifying within participating schools, what types of drinks are sold at the school (eg canteen and/or vending machines) and what is their closest access point to external sources of SSBs, as measured in walking distance. Given the recent introduction of the NSW Healthy Canteen Strategy, it is expected that the availability of SSBs in the canteen will be increasingly limited.

Data will be also be collected from Arms 1 and 3 regarding the acceptability of the TCW-BI from the perspective of immunisation staff and teachers via a short survey.

#### Statistical analysis plan

Descriptive statistics will be used to summarise study variables. Categorical variables will be reported as counts and proportions. If normally distributed, continuous variables will be presented as means and standard deviations. Otherwise, they will be presented as medians and interquartile ranges.

Baseline characteristics of study arms will be compared to assess similarity at study entry, thereby allowing for the identification of significant imbalances requiring adjustment during analysis. If continuous, differences will be assessed using two-sample t-test or Mann-U Whitney tests for data with non-normal distributions. Categorical variables will be analysed by Pearson chi-squared tests or Fisher’s exact test.

To account for clustering at the LHD and school level and the capture of longitudinal data, multi-level regression models with mixed effects will be developed to estimate interventional effect. For each model building process, variables found to be significantly associated with the outcome measure in the univariable analysis at the 10% level will be retained in the final model. As the primary predictor of interest, intervention effect will be forced into the multivariable model in the form of 4-level categorical variable. Continuous outcome measures will be analysed using linear regression models. For binary outcome measures, analysis will be by binary logistic regression, while multinominal logistic regression will be used to analyse non-binary categorical measures. Diagnostic testing will be conducted on all models to ascertain validity. Each model will be tested for violations of model assumptions, existence of influential points and goodness of fit. Tests for all outcomes will be two-tailed, with levels of statistical significance set at 5%. Statistical analysis will be performed using Stata 15.0 (StataCorp LP, College Station, Texas) statistical software.

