### Setting

The study will be conducted in secondary schools (including non-private and private schools) that are within the boundaries of three NSW Local Health Districts (LHDs)(Central Coast, Illawarra Shoalhaven and South West Sydney LHDs). Two of these LHDs are similar in characteristics, which similar population demographics, distance from the hub of Sydney and numbers of secondary schools within them. The third LHD has a significantly higher population, greater diversity and a higher number of schools. To allow the study to progress within these settings ethical approval was obtained through the Hunter New England Human Research Ethics Committee (17/08/16/4.07), the NSW Department of Education (SERAP2017457) and Broken Bay, Sydney and Wollongong Catholic Diocese.

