### Sample

All eligible schools within the boundaries of the three participating Local Health Districts will be invited to participate in the study, with the aim of recruiting 60 schools to the trial and randomly allocating 15 schools to each study arm. A sample of 60 schools will be selected from the three LHDs using a proportional stratified sampling technique. All year 7 students at recruited schools will be invited to participate. Schools that already have adequate working chilled water stations in situ (deemed to be one per 300 students) will be excluded from participating in the study. There is limited evidence regarding the ratio of chilled water stations per student, with the figure for this study being informed by guidance from US literature [15, 17, 18] and in consultation with the NSW Department of Education. Schools for special purposes for example schools for students with behavioural difficulties will be excluded from selection.

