### Recruitment and study participation

An initial email sent to all eligible schools will inform them of the study. Schools responding to this email expressing interest in the study will be contacted via telephone/email to arrange a follow-up meeting. At this meeting schools will be fully informed of the study protocol, and provided with the study information and consent form. If the school wishes to participate in the study, school level consent will be gained by the principal providing signed consent. Participation of students in the evaluation component of the study will be through an opt-out consent process, where parents must provide written documentation to state they do **not** wish their child to participate in the evaluation (except in Catholic schools within one Catholic Diocese, where an opt-in process will be mandatory).

Simple random sampling will be used to select from the pool of consenting schools, the requisite number of schools within each LHD required for inclusion in the study. Once 60 schools are identified for the study sample randomisation of the schools to the study arms will take place. Schools will be randomised by the study statistician using a computerised random number generator. Subsequently, principals will be informed of which study arm they have been allocated to. Those who were not included in the study sample will be informed of this. Following randomisation, baseline measures will be taken, interventions implemented and post and follow-up data collected as per Fig. 1 Flowchart of the study.

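### LHD is handled as a clustering level with only three units; it should be a pre-specified fixed effect, and the article should say whether allocation is stratified by LHD

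*Protocol article*

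**What the plan says.** **Analysis.** The *Statistical analysis plan* section of the protocol article specifies mixed-effects multilevel models "To account for clustering at the LHD and school level" and for the repeated measurements. Only the four-level intervention variable is forced in. Other covariates enter if they pass a univariable screen at the 10% level, and baseline comparisons between arms are to flag imbalances that need adjustment. LHD is not named as a fixed covariate.

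**The LHDs.** *Setting* places the schools "within the boundaries of three NSW Local Health Districts (LHDs" and names all three. Two are described as similar. Of the other it says: "The third LHD has a significantly higher population, greater diversity and a higher number of schools".

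**Sampling and allocation.** *Sample* states that "A sample of 60 schools will be selected from the three LHDs using a proportional stratified sampling technique", "with the aim of recruiting 60 schools to the trial and randomly allocating 15 schools to each study arm". *Recruitment and study participation* says that simple random sampling will select "the requisite number of schools within each LHD required for inclusion in the study". For allocation it says only: "Schools will be randomised by the study statistician using a computerised random number generator". No stratum, block or balancing factor is named for that step.

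**The concern.** Three named districts, picked by design and acknowledged to differ, are not a sample from a population of districts. A between-district variance estimated from three units is very imprecise. When its estimate is at or near zero, the model behaves as if LHD were not there, and nothing in the output need draw attention to this. Nothing else in the plan secures the adjustment: LHD could return as a covariate only through a baseline significance test or the 10% screen, and both depend on the data.

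This matters most if chance puts more large-LHD schools in one arm than in another. The article uses LHD to structure the sampling but describes no such structure for the allocation, so a reader cannot tell whether that imbalance is prevented. If it is not, the comparison of arms carries part of any difference in water drinking between districts.

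**Working it through.** **1. The plan's own figures (*Sample size calculation*).** These supply the ICC, cluster size and target used below.
- One-sample test of 40% against 45%, two-sided 5%, power 80%: n = (1.96·√(0.40·0.60) + 0.8416·√(0.45·0.55))² / 0.05² = 761.
- Design factor: 1 + (135 − 1)·0.055 = 8.37.
- 761 × 8.37 ≈ 6370 students; 6370/135 = 47.2, so 48 schools; 48/0.8 = 60.

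All the stated figures reproduce. The ICC is a school-level value, and no LHD component is given.

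**2. Precision of a three-unit variance.** With 3 − 1 = 2 df, the chi-square 2.5% and 97.5% points are 0.0506 and 7.378. The 95% interval for the variance runs from 2/7.378 = 0.27 to 2/0.0506 = 39.5 times the estimate. This describes the nuisance variance, not the treatment effect; step 4 covers the latter.

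**3. Chance imbalance if 60 schools are allocated 15 per arm without restriction.** The number of large-LHD schools, K, is not given, so K = 20 to 36 is assumed. The exact hypergeometric probability that one given arm differs from control is:

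| K | difference ≥ 4 of 15 | difference ≥ 5 of 15 |
|---|---|---|
| 20 | 17.8% | 8.2% |
| 24 | 19.5% | 9.5% |
| 30 | 20.4% | 10.2% |
| 36 | 19.5% | 9.5% |

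Across all four arms, the median gap between the arms with most and fewest large-LHD schools is 4 in simulation. A gap of 8 or more occurs in 2–3% of allocations.

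**4. What a random LHD intercept does about it.** School means were simulated with no treatment effect.
- Assumed respondents per school: 135 × 0.8 = 108.
- SD of a school mean: √(0.24·(0.055 + 0.945/108)) = 0.124.
- SE of an arm-versus-control difference: 0.124·√(2/15) = 0.045, or about 4.5 points.
- Assumed LHD split: 15/15/30, with the large LHD differing from the other two by a set amount.

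The LHD variance was estimated at about zero in 63% of runs when the LHDs do not differ, and in about 48%, 31% and 3% when the large LHD differs by 3, 5 and 10 points.

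The next table takes only allocations where the arm holds at least 5 more large-LHD schools than control (6,000 runs per row):

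| True LHD difference | Bias, no LHD term | Bias, random LHD | Bias, fixed LHD | Type I error, random | Type I error, fixed |
|---|---|---|---|---|---|
| 3 points | 1.2 | 0.6 | 0.0 | 5.8% | 5.4% |
| 5 points | 2.0 | 0.9 | 0.0 | 6.4% | 5.5% |
| 10 points | 3.8 | 0.8 | 0.0 | 6.1% | 5.5% |

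Hand check of the no-LHD column: a gap of exactly 5 schools and a 5-point difference give 5/15 × 5 = 1.7 points. The simulated 2.0 is higher because gaps above 5 are included.

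The random intercept therefore removes roughly half of the bias at 3–5 points and about four-fifths at 10 points. Over all allocations, balanced or not, its type I error is 4.9–5.5%.

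**The case against.** **Allocation.** A reader might infer that the randomisation is not stratified by LHD. The article does not say so. It is a condensed report, stratification details are commonly left to the full protocol, and the target of 15 per arm already implies some restriction beyond a bare random number generator. This stands: the point can only be that no stratification is described. It does not remove the modelling point, because a stratification factor would also belong in the model.

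**Random term.** The article does not say in terms that LHD is a random effect, and a mixed model has both kinds. That is fair, but naming LHD alongside school as a level of clustering is most naturally read as a random level, and no fixed LHD term is secured elsewhere.

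**Correction.** A reader might infer that the model cannot correct an imbalance. The figures do not support that. The variance estimate falls to zero mainly when there is little to correct, and the residual bias is under 1 point beside a pairwise standard error of about 4.5.

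**Baseline data.** If the longitudinal model estimates change from baseline by arm, stable level differences between LHDs largely cancel. This also stands. The calculation uses a single occasion, so it overstates the bias for such a model. The article does not state the arm-by-time form, so the reduction cannot be assumed.

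**Conclusion.** The point holds as a modelling weakness of minor to moderate size. Three purposively chosen, differing LHDs are a poor basis for a variance component. A fixed effect removes the conditional bias that a random intercept leaves behind: about 0.6–0.9 points, up to nearly a fifth of the 5-point target, given an arm-versus-control gap of 5 or more schools. If allocation is unrestricted, such a gap in either direction has a probability of about 8–10% for a given arm.

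Stronger readings are not supported. Severe imbalance is uncommon, since a gap of 8 or more of 15 between the extreme arms occurs in 2–3% of allocations. Overall type I error stays near 5%. Convergence failure of the logistic models is possible but has not been shown.

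The sizes rest on assumed LHD splits, assumed differences between LHDs, 108 respondents per school, and a linear model of school means in place of the planned longitudinal logistic model. The case for a fixed effect depends on none of these: it follows from there being three chosen districts.

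**What to change.** 1. Pre-specify LHD as a fixed effect in every outcome model, forced in alongside the intervention term and exempt from the 10% screen and the baseline tests. Keep random intercepts for school and for student across waves. The cost is 2 degrees of freedom; the sample size arithmetic, the data collected and the number of schools do not change. This applies even if allocation is complete.
2. State whether allocation is stratified by LHD. If it is still open, stratify it by LHD, which is known for every school beforehand. Counts per LHD would then differ between arms by about one school at most.
3. Do not add school sector as a further blocked stratum. Three LHDs by three sectors give up to nine strata for 60 schools, and incomplete blocks could upset the 15 per arm.

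### Adjustment covariates are chosen from the trial data, by baseline significance tests without cluster correction and by a univariable 10% screen, instead of being fixed in advance

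*Protocol article*

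**What the plan says.** All of this is in the protocol article, mostly under Statistical analysis plan.

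- **Baseline tests.** The arms are compared at study entry, "thereby allowing for the identification of significant imbalances requiring adjustment during analysis". For continuous variables, "differences will be assessed using two-sample t-test or Mann-U Whitney tests for data with non-normal distributions". For the rest, "Categorical variables will be analysed by Pearson chi-squared tests or Fisher’s exact test". Clustering is brought in only in the next paragraph, for the multi-level outcome models.
- **Univariable screen.** In each model-building process, variables "significantly associated with the outcome measure in the univariable analysis at the 10% level will be retained in the final model".
- **Intervention term.** The "intervention effect will be forced into the multivariable model in the form of 4-level categorical variable", so the screen cannot drop it.

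No covariate is named in advance. LHD appears only as a level of clustering. The candidates for the screen are not limited to variables measured before the intervention. Table 1 (Outcomes) lists knowledge, attitudes and purchasing as secondary outcomes, along with "The school environment eg promotion of water messages, reduced access to SSBs". The Data collection section repeats the same student survey at all three time points. Under Recruitment and study participation, baseline is measured after randomisation, once principals have been told their arm.

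**The concern.** Schools are randomised, so any true baseline difference between arms is chance, and a p-value is the wrong trigger for adjustment. A student-level test that ignores clustering makes this worse, because it calls ordinary between-school variation a significant imbalance.

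The 10% screen has a different fault. It uses the outcome data to decide the model, so the adjustment set can differ from one outcome to the next and is unknown until the data are seen. The two rules can also disagree: a variable may be imbalanced yet fail the screen, or pass it while balanced. The text gives no precedence.

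Finally, nothing in the rule keeps out a variable that the interventions are meant to change. At stake are a fixed, reproducible primary estimate and, in the worst case, part of the effect itself.

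**Working it through.** **Inputs.** From Sample size calculation: ICC 0.055, 135 students per school, 20% non-response, design effect 8.37. From Sample: 60 schools, 15 per arm. From Statistical analysis plan: two-sided 5%.

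**The plan's own design effect.** 1 + (135 − 1) × 0.055 = 8.37, as stated. With 20% non-response, 135 × 0.8 = 108 per school, and 1 + 107 × 0.055 = 6.885.

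**Two-group baseline test without cluster correction.** The variance of the difference is larger than the test assumes by the design effect (DE). The chance of flagging a true null is therefore 2 × [1 − Φ(1.96/√DE)], whatever the number of schools per group.

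| ICC | Students per school | DE | 1.96/√DE | Flagged |
|---|---|---|---|---|
| 0.055 | 108 | 6.885 | 0.747 | 45.5% |
| 0.055 | 135 | 8.37 | 0.677 | 49.8% |
| 0.01 (assumed) | 135 | 2.34 | 1.281 | 20% |
| 0.02 (assumed) | 135 | 3.68 | 1.022 | 31% |
| 0.10 (assumed) | 135 | 14.4 | 0.517 | 61% |

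Beta-binomial simulation (20,000 runs) gave 45.9% and 49.9% for the first two rows.

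**Four-arm chi-squared test (3 df).** P(χ²₃ > 7.815/DE) is 76.9% at DE 6.885 and 81.7% at DE 8.37. Simulation gave 77.0% and 82.4%.

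**Screen at 10%.** With an assumed 10 independent noise candidates and a valid test, the chance of keeping at least one is 1 − 0.9¹⁰ = 65%.

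**Effect of the screen on the intervention estimate.** The simulation used 60 schools, four arms, no intervention effect, 10 or 20 school-level noise candidates, 108 students per school and ICC 0.055, with 4,000 runs per setting.

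- Type I error for an arm effect was 4.6% to 5.4%, so there was no inflation.
- With no covariates, the SD of the estimate (outcome SD 1) is √[(0.055 + 0.945/108) × 2/15] = 0.092.
- With a screen that respects clustering, it was 0.089 for both 10 and 20 candidates.
- With a screen that ignores clustering, it was 0.093 with 10 candidates and 0.098 with 20. The latter is about 6% above the no-covariate value (0.098/0.092).

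**If a post-intervention mediator entered.** In a linear model with no mediator–outcome confounding, the adjusted effect is the total effect times (1 − mediated share). For 5 points and assumed shares of 25%, 50% and 75%, this gives 5 × 0.75 = 3.75, 5 × 0.50 = 2.5 and 5 × 0.25 = 1.25 points. Simulation gave 3.6, 2.5 and 1.3.

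**The case against.** The strongest defence is that the trial's inference does not rest on the baseline tests. The outcome model handles clustering, the intervention term is forced in, and screening among true baseline noise left the type I error at its nominal level with little or no loss of precision. This stands, and it limits the harm. A reader might take the 46% to 82% as false-positive rates of the trial; they are only rates at which a chance difference is flagged.

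The rates also use an ICC estimated for water consumption. Other student variables may have a smaller one, hence the range. They do not apply to school type, size, FOEI, canteen or vending machines tested with schools as units, where there is no within-school clustering to ignore. The text does not state the unit of the baseline tests, nor whether the univariable screen is fitted with the mixed model. The clustering fault can therefore be shown only for the named baseline tests when applied to student variables.

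A reader might also infer that knowledge, attitudes or purchasing will be adjusted for and the effect removed. The document does not say so. It never names them as candidates, and the paragraph before the screen discusses adjustment only for baseline characteristics. The text permits mediator adjustment but does not plan it.

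It could be said that a candidate list belongs in a fuller plan. That would excuse a missing list, but not the two selection rules, which the article itself fixes.

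**Conclusion.** The point holds as a badly fixed rule. Both routes make the adjustment set depend on the data, and neither criterion suits a randomised comparison. For student-level variables at ICC 0.055, chance imbalance would be flagged in about 46% to 50% of two-group tests and 77% to 82% of four-arm tests. For assumed ICCs of 0.01 to 0.10 at 135 per school, the two-group range is 20% to 61%.

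The demonstrated cost to the intervention estimate is modest: a model not settled in advance, and an SD up to about 6% larger in the least favourable setting simulated. Inflated type I error is not shown. Attenuation by a mediator is a conditional risk, and its size rests on assumed mediated shares. The change should be made, but the rules do not by themselves invalidate the analysis.

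**What to change.** Delete both selection rules. Name a short list of pre-intervention covariates, the same in every model and kept regardless of p:

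- the baseline value of the outcome, or baseline handled as a repeated measure in the longitudinal model;
- LHD, stating how this fits with its present role as a clustering level;
- school type and FOEI, both in the school profile;
- sex, only if it is collected, since the Data collection section does not list it for students.

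Bar any variable measured after the intervention starts. The limit should be worded as pre-intervention, not pre-randomisation: baseline is taken after allocation, so the stricter wording would exclude the baseline outcome. Present baseline characteristics by arm descriptively, without p-values.

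The cost is a change of analysis wording, best made before outcome data are seen. No new data and no change to the sample size are needed.
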